## Abstract

**Introduction:**

The National Institute for Health and Care Excellence (NICE) guidelines for attention deficit/hyperactivity disorder (ADHD) state that young people need to have access to the best evidence-based care to improve outcome. The current ‘gold standard’ ADHD diagnostic assessment combines clinical observation with subjective parent, teacher and self-reports. In routine practice, reports from multiple informants may be unavailable or contradictory, leading to diagnostic uncertainty and delay. The addition of objective tests of attention and activity may help reduce diagnostic uncertainty and delays in initiating treatment leading to improved outcomes. This trial investigates whether providing clinicians with an objective report of levels of attention, impulsivity and activity can lead to an earlier, and more accurate, clinical diagnosis and improved patient outcome.

**Methods and analysis:**

This multisite randomised controlled trial will recruit young people (aged 6–17 years old) who have been referred for an ADHD diagnostic assessment at Child and Adolescent Mental Health Services (CAMHS) and Community Paediatric clinics across England. Routine clinical assessment will be augmented by the QbTest, incorporating a continuous performance test (CPT) and infrared motion tracking of activity. The participant will be randomised into one of two study arms: QbOpen (clinician has immediate access to a QbTest report): QbBlind (report is withheld until the study end). Primary outcomes are time to diagnosis and diagnostic accuracy. Secondary outcomes include clinician's diagnostic confidence and routine clinical outcome measures. Cost-effective analysis will be conducted, alongside a qualitative assessment of the feasibility and acceptability of incorporating QbTest in routine practice.

**Ethics and dissemination:**

The findings from the study will inform commissioners, clinicians and managers about the feasibility, acceptability, clinical utility and cost-effectiveness of incorporating QbTest into routine diagnostic assessment of young people with ADHD. The results will be submitted for publication in peer-reviewed journals. The study has received ethical approval.

**Trial registration number:**

NCT02209116.

Strengths and limitations of this studyA pragmatic diagnostic randomised controlled trial design in standard National Health Service (NHS) settings.The focus of the trial is the impact of an objective assessment technology on clinical decision making and patient outcomes.There is limited data regarding the clinical utility, cost-effectiveness and acceptability of using the QbTest to aid attention deficit/hyperactivity disorder assessment and treatment.

## Introduction

Attention deficit/hyperactivity disorder (ADHD) is the most common neurodevelopmental disorder and affects 3–5% of children and young people.^1^ The core symptoms of ADHD include poor attention, hyperactivity and impulsivity. National Institute for Health and Care Excellence (NICE)^1^ guidelines provide a blueprint for the diagnosis and management of ADHD in England and Wales and indicate the need for young people with ADHD to have access to the best evidence-based care in order to fulfil their potential and prevent poor outcome. However, in practice, delivery and quality of care is ad hoc, with little consistency in assessment, diagnosis or management.^2^ ADHD frequently coexists with other neurodevelopmental and psychiatric disorders and is a risk factor for major educational, social and occupational impairment, placing a huge burden on the National Health Service (NHS), social care and criminal justice systems. There has been a rapid growth in diagnosis over the past 30 years with the number of children recognised and treated for ADHD in the UK increasing almost 10-fold from the early 1980s^1^ and spending on medication for ADHD increasing sevenfold between 1998 and 2005.^3^ The cost of initial specialist assessment for ADHD is estimated at £23 million annually in England and Wales^4^ and drug costs for ADHD in England during 2012 was expected to exceed £78 million^3^ while indirect costs to families include parental mental ill health, time off work and loss of earnings are even higher.^5^ Increasing recognition of ADHD as a lifespan condition is placing a new demand on the NHS to provide diagnostic and treatment services for children, adolescents and adults, exposing serious limitations in existing methods of assessment and management.

There is no single test, or biomarker used to diagnose the disorder.^6^ In the absence of any objective measure to identify ADHD, clinical assessment and diagnosis is based on the clinician's integration of various forms of subjective information including direct observation and reports from parents, teachers and young people. This approach is heavily reliant on subjective measures and clinical interpretation, which can lead to lack of reliability and consistency in the diagnosis of ADHD^7^ and furthermore, the process of ‘gold standard’ clinical interviews and data collection from multiple informants is time consuming and often difficult to conduct in real world settings with frequent missing data and inconsistencies between reports leading to and diagnostic uncertainty and delay.

Additionally, while treatments for ADHD are highly efficacious in carefully managed research settings^1^ in standard community care the outcome of treatment may be suboptimal. Aside from delays in initiating treatment caused by diagnostic uncertainty, once on medication, children may not be reviewed sufficiently frequently for clinicians to detect non-response or partial response, or to establish the optimal dose for each child. The US National Institute of Mental Health (NIMH) Multimodal Treatment study of ADHD (MTA) showed that careful medication management can significantly improve outcomes, doubling the normalisation rate from 25% in routine community care to almost 60% when using a strategy of careful dose titration and frequent monitoring of outcome.^8^ The NICE^1^ ADHD guidelines recommends that during the titration phase, symptoms should be closely monitored using rating scales. However, audit data within the East Midlands showed that community care for ADHD falls well below the standards for titration and monitoring set out in the MTA and NICE guidelines (CLAHRC-NDL, 2013, unpublished audit). A further consequence of suboptimal treatment response in routine care is poor medication adherence. In the UK, 50% of patients have stopped ADHD medication after 18 months and 80% after 3 years.^9^

### Objective assessment measures in ADHD

One approach to improving assessment and outcomes in routine care is to add objective laboratory measures of activity and attention for diagnostic assessment and treatment optimisation.^5^ Objective measures have the potential to augment and streamline current practice in order to shorten assessment time, increase diagnostic accuracy, reduce delays in treatment and optimise treatment response.

### Continuous performance test

A continuous performance test (CPT) is a neuropsychological test that measures the individual's capacity to sustain attention (vigilance) and inhibit inappropriate responses (impulsivity), which can be used alongside clinical evaluation to inform the diagnostic process.^10^ Typically, a CPT is a computer-based programme which involves rapid presentation of visual or auditory stimuli. Participants are asked to respond when a given target occurs but remain passive to non-targets. A standard CPT typically records the child's omission errors (responding when the target is present), commission errors (responding when the target is not present), number of correct responses, reaction time and variability in reaction time. There are several well validated commercially available CPT tests such as the TOVA (Test of Variables of Attention^11^), IVA (Integrated Visual and Auditory^12^), ACPT (Auditory CPT^13^) and the Conner's CPT.^14^ These tests are one of the most popular clinic-based measures to assess sustained attention in children;^15^ with several studies and a meta-analyses showing that children with ADHD perform worse on these tasks than children without ADHD.^16^ CPTs have also been shown to be a sensitive measure of medication effects.^17^ Several studies have noted improvement in CPT scores in children with ADHD on stimulant medication.^15^
^18–20^ However, little research has compared CPT scores with more subjective measurements of ADHD^7^ and in their recent review Ogundele *et al*^7^ recommended further research in the use of CPTs compared to standard practice to determine cost-effectiveness of these tasks.

A significant limitation of the CPT for the assessment of ADHD is that it does not measure the patients’ activity levels, which is a core symptom domain of ADHD. Approaches to the objective measurement of activity in ADHD have included wrist-worn actigraphy devices and infra-red motion capture.

### QbTest

QbTest (Qbtech Ltd) has been developed to combine a CPT to measure attention and impulsivity with infra-red motion capture of head movement during the CPT to measure activity.^21^ The QbTest CPT requires participants to respond to an infrequently presented stimulus (by pressing a button) but ignore all others. Physical activity is measured during the course of the CPT via an infra-red camera that tracks the path of a reflector attached to the participants head (central midpoint). These elements of the test provide information on each of the three symptom domains of ADHD and provide summary scores for each individual based on deviation from a normative data set based on age group and gender. There are two versions of the task for children and young people; the task for 6–11-year olds is 15 min duration and the task for 12–17-year olds is 20 min duration. The QbTest result is complemented by a clinical evaluation and behavioural observation of events that may affect test performance. The QbTest is not a stand-alone diagnostic tool, but has been approved by the US Food and Drug Administration (FDA; Ref: K133382) to supplement standard clinical assessment and treatment follow-up by reducing reliance on measures such as subjective observer reports (which can be biased, incomplete or missing) and augment clinical decision-making.

The data available about the QbTest has shown favourable psychometric characteristics with child participants. For example, Qbtech report data that establishes 85% sensitivity of classification and 92% specificity, and good test–retest scores, which is not influenced by experience with computers ([name], 2012, unpublished data). Reh *et al*^22^ investigated the factor structure and concurrent and discriminant validity of QbTest and found the hyperactivity factor correlated with teacher ratings of hyperactive behaviour, providing evidence for the utility of including this additional measure of activity in a CPT. In addition, Reh *et al*^23^ found the hyperactivity factor could identify intermediate levels of impairment in ADHD siblings, suggesting this factor maybe particularly sensitivity as an intermediate phenotype for ADHD. Their findings also provide initial evidence for the concurrent validity of the three factors (attention, impulsivity and activity), although the authors highlight the need for further research to investigate validity. Wehmeier *et al*^24^ found QbTest to be a valid measure of treatment outcome and highly correlated with blinded observer ratings of behaviour in placebo-controlled randomised controlled trial (RCTs). QbTest is effective in evaluating ADHD medication effects in children^25^
^26^ and can identify early non-responders.^15^ One clinical study found QbTest improved clinical accuracy by reducing the risk of unidentified ADHD when patients were re-evaluated 1 year after their initial assessment^27^ and another indicated the ability for QbTest to differentiate ADHD from normative controls.^28^ Initial audit data ([name], 2013, unpublished data) suggest that implementation of QbTest in routine ADHD clinics can reduce the time to diagnosis by 30%. This equates to a reduction from an average of three to two out-patient appointments per patient in order to either confirm or exclude a diagnosis of ADHD. These findings indicate potential for QbTest to support the diagnostic assessment and management of ADHD within routine clinical practice; however, there has been no RCT to investigate the added clinical value (clinical utility) and economic cost-effectiveness of adding QbTest to standard ADHD care pathways within the NHS.

The primary aim of the *A*ssessing *Q*bTest *U*tility in *A*DHD-Trial (AQUA-Trial) is to determine whether using QbTest in routine NHS settings can accelerate diagnosis without compromising diagnostic accuracy. Second, the study aims to examine whether QbTest improves the medication titration process by increasing the proportion of patients normalised after 6 months postbaseline assessment and improves patient outcome. The study will also use qualitative methods to explore the barriers, drivers and facilitators to the adoption of the QbTest in routine practice. The cost-effectiveness of implementing the QbTest in practice will also be investigated. The findings will indicate whether establishing QbTest as part of standard practice in ADHD assessment and management is clinically useful, financially viable and acceptable for clinicians and patients.

## Methods and analysis

### Trial design

This study is a parallel group single-blind multicentre RCT, exploring feasibility and acceptability, using quantitative and qualitative and health economic evaluations. The study consists of two arms:
QbOpen (QbO): In this arm of the trial participants will complete the QbTest and clinicians, participants and their families will have immediate access to a QbTest report.QbBlind (QbB): In this arm of the trial participants will complete the QbTest but the QbTest report will be withheld from the clinician, participant and patient's family until the last outcome measure is completed at 6 months. All participants will receive the same intervention. Specifically, this will be assessment as usual plus a QbTest as part of the diagnostic assessment.

The patients usual care team will be responsible for conducting the QbTest in clinic appointments. The QbTest will be only be conducted by trained QbTest clinicians.

### Setting

Child and Adolescent Mental Health Services (CAMHS) and Community Paediatric clinics across nine different NHS Trusts in England, including Medway NHS Foundation Trust, Alder Hey Children's NHS Foundation Trust, Nottinghamshire Healthcare NHS Trust, Leicestershire Partnership NHS Trust, Sussex Partnership NHS Foundation Trust, United Lincolnshire Hospital NHS Trust, Central Manchester University Hospitals NHS Foundation Trust, Bridgewater Community Healthcare NHS Trust, Nottingham University Hospitals NHS Trust. Additional NHS Trusts may be recruited to meet target recruitment figures.

### Recruitment and eligibility

New referrals for a diagnostic evaluation for suspected ADHD will be invited to participate in the research based on the following criteria:

*Inclusion criteria*
Age 6–17 years old (at the time of consent);Referred to CAMHS or Community Paediatrics for an ADHD diagnostic assessment;Capable of providing written informed consent (over 16 years old);Parental consent (under 16 years old).

*Exclusion criteria*
Severe learning disability (to be assessed by clinical judgment);Non-fluent English speaking;Previous or current confirmed diagnosis of ADHD;Currently receiving ADHD medication.

Written information about the trial will be sent to families through the clinic administrators prior to their first appointment. Clinic invitations will be updated and recorded on a password protected database on a weekly basis. Parents and young people who wish to participate will be asked to complete and return a consent form before this appointment. Alternatively, participants will be consented into the study by the clinical team, clinical studies officer or a member of the research team at their first appointment. Each site will be informed of the monthly recruitment target required in order to meet the study sample size and updated on their monthly progress.

### Trial phases

There are two phases to this study (figure 1).

**Figure 1 BMJOPEN2014006838F1:**
[figure not shown]
Study flow chart. ADHD, attention deficit/hyperactivity disorder; CAMHS, Child and Adolescent Mental Health Services.

Phase 1, Assessment: The first phase investigates the use of QbTest as a tool to aid diagnosis. Participants will undergo ADHD ‘assessment as usual’, which varies between clinics, clinicians and cases, but will typically involve an interview with the parent/young person and collection of questionnaires from the parent/young person and teacher. While attending the clinic, the participant will be asked to complete the QbTest at some point during the diagnostic process. Participants will also be asked to complete baseline outcome measures (see measures section).

Phase 2, Treatment: Patients who receive a clinic diagnosis of ADHD and are allocated by clinicians to receive ADHD medication initiated within 3 months of their baseline assessment will be asked to complete a second QbTest (Qb2) 4–8 weeks after medication initiation. This timeframe was chosen to ensure that all participants can complete their second QbTest before the 6-month follow-up.

All participants will stay in the trial for 6 months and will be asked to complete outcome measures at 3 and 6-month follow-up, regardless of their diagnosis or whether they receive medication. With the aim of promoting participant retention and completion of follow-up measures, participants will be compensated for their time with a £15 high-street voucher if they remain in the trial until 6 months.

### Measures

Blinded members of the research team ([name], [name], [name],) will be fully trained in all trial assessments and responsible for monitoring the distribution, completion and collection of all outcome measures.

#### Primary outcome

The primary outcome is the number of consultations until a confirmed clinical diagnosis is reached, as recorded on a short pro-forma. The pro-forma will be completed by clinicians after each consultation with the young person and/or family and documents information about appointment duration, diagnosis and medication/treatment. The pro-forma can be provided by contacting the corresponding author.

#### Secondary outcomes

The secondary outcomes obtained from the pro-forma are:
Number of days and duration of visits (in minutes) until a confirmed diagnosis is reached.Clinical confidence in diagnostic decision. Clinicians will be required to rate the confidence of their decision on a 7-point Likert scale (Definitely ADHD-Definitely not ADHD).Stability in diagnosis. Clinicians will be required to re-rate their diagnostic decision and confidence at 6 months.

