### Data analysis plan

The analysis will be conducted on an intention-to-treat (ITT) basis. Exploratory analysis will be conducted first for outcome and patient background variables; descriptive statistics of each variable will be presented separately for each group at each follow-up point, with means and SD for normally distributed variables, medians (IQR) for skewed variables and frequency (percentage) for categorical variables. Missing values will be checked and reported. Multiple imputation will be used to hand missing values, based on a multilevel modelling approach.

To compare the number of visits needed to achieve an ADHD diagnosis (either confirmed or excluded) between groups, Poisson regression with binary group status as the explanatory variable will be implemented. To compare clinician's confidence in their diagnostic decisions, multilevel modelling with patient as a level 2 unit will be used to take into account the non-independence within patient data due to repeated measures.^41^

κ Statistics will be used to reflect the stability of diagnosis between first confirmed diagnosis and diagnosis rerated at 6-month follow-up time. κ Statistics will be reported for each group and the stability of diagnosis will be compared between arms using logistic regression. The same analysis approach will be implemented to explore the stability of diagnosis confidence between time of first confirmed diagnosis and 6-month follow-up. To assess the diagnosis accuracy, the sensitivity, specificity, likelihood ratio (LR) ve+, LR ve−, positive predictive value (PPV) and negative predictive value (NPV) will be reported for each group and the test performance will be compared between QbO and QbB arms.^42^
^43^ Receiver operating characteristic curve analyses will be used to obtain the best predictive model based on QbTest scores that discriminates between ADHD ‘positive’ and ADHD ‘negative’ gold standard DAWBA diagnoses.

For treatment related outcomes (phase 2) outcome measures such as SNAP-IV, side effects scale, SDQ and C-GAS scores, multilevel modelling with patient as a level 2 unit will be again applied to quantify the difference between QbO and QbB arms.

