For time to event variables such as time to diagnosis (in days), survival analysis using log-rank test will be performed for group comparison and Kaplan-Meier survival curves will be displayed for each group. Logistic regression will be used to compare the proportion of normalisation between two groups at 6-month follow-up time. For all regression modelling to explore the difference between arms, group status will be included as explanatory variables. Data transformation would be needed for skewed outcome variables.

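### The 7-point confidence rating mixes the direction of the diagnosis with certainty, and no recoding is stated before it is compared between arms

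*Protocol article*

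**What the plan says.** Under Secondary outcomes, the protocol article names the construct as "Clinical confidence in diagnostic decision" and defines it by one item: "Clinicians will be required to rate the confidence of their decision on a 7-point Likert scale (Definitely ADHD-Definitely not ADHD". The next item on that list has clinicians rate decision and confidence again at 6 months.

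The Data analysis plan gives the model: "To compare clinician's confidence in their diagnostic decisions, multilevel modelling with patient as a level 2 unit will be used". It adds a general rule for arm comparisons: "For all regression modelling to explore the difference between arms, group status will be included as explanatory variables". The only rescaling mentioned is "Data transformation would be needed for skewed outcome variables". The same section makes clear that ADHD may be confirmed or excluded, so ratings are expected towards both ends of the scale.

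Under Primary outcome, the clinic pro-forma "documents information about appointment duration, diagnosis and medication/treatment". The diagnosis is therefore available alongside the rating.

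**The concern.** A clinician who is sure of ADHD and one who is sure there is no ADHD are equally confident, yet they score at opposite ends. In an average of the raw rating they offset each other. A model of that rating on group status estimates how far one arm's decisions lean towards ADHD compared with the other's, weighted by certainty. That is not the named construct.

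Two errors follow. A real gain in certainty is shrunk, cancelled or given the opposite sign, depending on the mix of diagnoses. A change in the mix alone is read as a change in confidence. Reducing diagnostic uncertainty is the trial's rationale, and clinician confidence is the first secondary outcome named in the abstract. The second error is a live possibility because the trial tests whether the report changes clinical decisions.

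**Working it through.** **Inputs from the article.** A 7-point scale with the two end anchors; a multilevel model with group status as explanatory variable; 71 patients per group; 178 in total as a minimum and 234 as a maximum. The article states no effect size or power for confidence.

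**The plan's own figure.** The 71 per group is for the primary outcome, and it reproduces. On the log rate ratio, n = (1.960 + 0.842)² × (1/2.94 + 1/2.18) / [ln(2.94/2.18)]² = 70.1, so 71. Then 142/0.8 = 177.5, so 178. It is used below only as the number per arm.

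**Assumptions, because the article gives no figures.** Ratings are numbered 1 (sure of ADHD) to 7 (sure of no ADHD), with 4 as undecided. Certainty is c = |rating - 4|, from 0 to 3. The share judged to have ADHD, p, is varied. Two pairs of certainty distributions (percentages at c = 0/1/2/3) are tried:

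- Pair A: QbBlind 15/30/35/20, mean 1.60; QbOpen 8/20/37/35, mean 1.99; gain g = 0.39.
- Pair B: QbBlind 5/25/40/30, mean 1.95; QbOpen 2/13/35/50, mean 2.33; gain g = 0.38.

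**Step 1: what the raw mean measures.** If mean certainty m is the same for both diagnoses,

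mean rating = 4 - p·m + (1 - p)·m = 4 - (2p - 1)·m.

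**Step 2: a gain in certainty with the same p in both arms.** The arm difference is -(2p - 1)·g. Its size is 0 at p = 0.5, 0.2g at 0.6, 0.4g at 0.7, 0.6g at 0.8, 0.8g at 0.9 and g at 1. Below 0.5 the sign reverses. For pair B at p = 0.6 it is 0.2 × 0.38 = 0.08 points instead of 0.38.

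**Step 3: the raw rating is also more variable.** In pair A, QbBlind, the mean of c² is 0.30 + 1.40 + 1.80 = 3.50. The SD of c is √(3.50 - 1.60²) = 0.97. The SD of the raw rating at p = 0.6 is √(3.50 - (0.2 × 1.60)²) = 1.84.

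**Step 4: illustrative power.** Pair A, one rating per patient, t-test at two-sided 5%, 3,000 simulated trials per setting:

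| p | raw, 71 per arm | raw, 117 per arm |
|---|---|---|
| 0.5 | 5% | 5% |
| 0.6 | 6% | 6.5% |
| 0.7 | 8% | 9% |
| 0.8 | 13% | 18% |
| 0.9 | 26% | 36% |
| 1.0 | 69% | 87% |

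The folded score c has power of 66-69% with 71 per arm and 87-89% with 117 per arm at every p in the table. Pair B at p = 0.6 with 71 per arm (20,000 trials) gives 5.5% raw and 78% folded.

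**Step 5: equal certainty, different mix.** The arm difference has size 2 × (p₁ - p₀) × m. For 70% v 60% it is 0.2 × m:

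- m = 1.60: 0.32 points (0.31 in simulation), significant in 18% of trials with 71 per arm.
- m = 1.95 to 2.33: 0.39 to 0.47 points, significant in 20-21% of trials.

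The folded score rejects in about 5% of trials, as it should.

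**The case against.** The strongest reply is that the article never says the raw 1-7 score enters the model. It says confidence is compared, lists decision and confidence as separate items at 6 months, and records the diagnosis on the same form. Taking distance from the midpoint as confidence contradicts none of this. Deriving a score is ordinary analysis-plan content, and neither the analysis plan nor the pro-forma is shown. Only the end anchors are given, so the meaning of the midpoint is inferred. This stands as a limit on severity. It does not remove the point: the article fixes the construct, the instrument and the model, and those three followed literally yield the wrong estimand.

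A reader might go further and infer that the rating records which diagnosis was made rather than how sure the clinician was, and that the planned model cannot detect a gain. The documents do not support that. The rating carries both pieces of information, and certainty is recoverable from it. Complete loss occurs only at p = 0.5; elsewhere the gain is diluted, and at p = 1 nothing is lost.

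The sizes also rest on assumed diagnosis shares and certainty distributions. Nothing in the article says the arms will differ by 10 points in diagnosis rate. The power figures use one rating per child, while the plan has repeated measures.

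The stability analysis is a separate matter. The article says "The same analysis approach will be implemented to explore the stability of diagnosis confidence between time of first confirmed diagnosis and 6-month follow-up", which refers to kappa and logistic regression. Agreement on the signed rating is a legitimate measure there and does not cancel opposite ends. Folding would count a switch between the two extremes as fully stable. Which score to use there is a preference, not an error.

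**Conclusion.** The concern holds for the between-arm comparison of confidence. The item mixes direction with certainty and the article states no rule to separate them. Modelled as scored, the contrast keeps only the fraction |2p - 1| of a certainty gain, and a 70% v 60% difference in diagnoses appears as a confidence difference of about 0.3 to 0.5 points. The (2p - 1) factor assumes a linear model of the raw rating, the same p in both arms and the same gain for both diagnoses. It depends on neither the certainty distributions nor the choice of test. The power figures and the 0.3 to 0.5 range are illustrations under stated assumptions.

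Severity is moderate. This is a secondary outcome; the primary outcome, sample size and data collection are unaffected, and the unseen analysis plan may already score the item properly.

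**What to change.** Before unblinded results are seen, state in the analysis plan that, for the comparison of confidence between arms, the score is |rating - 4|, from 0 (undecided) to 3 (definite). Analyse it with a mixed model suited to an ordinal outcome, keeping the patient level for repeated ratings. Report the signed rating separately, as the direction of the decision. If the analysis plan already contains such a rule, it is enough to confirm it. The scoring used for stability of confidence can be left to the analysts.

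The cost is one sentence and no new data. The small downside is a coarser score with four levels.
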